**Informed consent**

The investigator assumes the responsibility of obtaining written informed consent for each patient or the patient's legally authorized representative before any trial-specific procedures are performed and before any trial drug is administered.

Patients meeting the criteria set forth in the protocol will be offered the opportunity to participate in the trial. To avoid introduction of bias, the investigator must exercise no selectivity with regard to offering eligible patients the opportunity to participate in the trial. Patients or parents/legal guardians of all candidate patients will receive a comprehensive explanation of the proposed treatment, including the nature of the therapy, alternative therapies available, any known previously experienced adverse reactions, the investigational status of the trial drug, and other factors that are part of obtaining a proper informed consent. Patients will be given the opportunity to ask questions concerning the trial, and adequate time to consider their decision to or not to participate.

Informed consent will be documented by the use of a written consent form that includes all the elements required by regulations and ICH guidelines. The form is to be signed and dated by the patient or patient's legally authorized representative and by the person who administers the consent process. A copy of the signed form will be given to the person who signed it, the original signed consent form will be filed with the patient's medical records. The date and time of the informed consent must be recorded in the source documents.

If an amendment to the protocol changes the patient participation schedule in scope or activity, or increases the potential risk to the patient, the informed consent document must be revised, submitted to the EC for review and approved by the EC before use. The revised informed consent document must be used to obtain re-consent from any patients currently enrolled in the trial if the patient is affected by the amendment, and must be used to document consent from any new patients enrolled after the approval date of the amendment.

### **Patient privacy**

The investigator affirms and upholds the principle of the patient's right to privacy. The investigators shall comply with applicable privacy laws.

### **Confidentiality**

The written informed consent form will explain that the trial data will be stored in a computer database, maintaining confidentiality in accordance with local data legislation and the EU directive 95/46/EG. Subjects in this database will be identified by patient identifier only. The patient information will also explain that for data verification purposes, authorized representatives of the sponsor, a regulatory authority, an ethics committee, or an institutional review board may require direct access to parts of the medical records relevant to the trial, including subjects' medical history.

Especially, anonymity of the patients will be guaranteed when presenting the data at scientific meetings or publishing them in scientific journals.

## **5.8 Enrollment into the trial**

### **Reporting and recruitment**

If after completion of staging the patient is qualified for the trial and he/she gives written informed consent, recruitment will be performed by LCGC in Köln. For recruitment, the following is required:

- all entry criteria satisfied;
- no exclusion criterion satisfied;
- staging procedures completed according to protocol.

Patients should be asked to agree to be contacted by the trials coordination center.

This agreement and the patient's address are to be recorded on the REG form.

Patients who wish to avoid sending their personal data to the trials coordination center may be enrolled anonymously under a pseudonym code. Prerequisite for anonymous enrollment is, however, commitment to follow-up and documentation.

## 5.9 Treatment

### Erlotinib ( Tarceva®)

The oral drug erlotinib (OSI-774, OSI pharmaceuticals; Tarceva®, Roche) is a small-molecule EGFR tyrosine kinase inhibitor.

Three phase-II single agent studies with erlotinib at 150 mg daily dose were performed (I) in patients with chemotherapy resistant, HER1/EGFR-expressing NSCLC of all histological subentities (Perez-Soler et al., 2004), (II) in patients with bronchoalveolar carcinoma previously untreated or treated with chemotherapy (Patel, 2003) and (III) as first-line therapy in elderly patients with NSCLC of all histological subentities (Johnson, 2004). The drug was well tolerated, drug-related cutaneous rash and diarrhea were observed in approximately two thirds of patients. The response rates were 12.3%, 25% and 13.3%, respectively. The median survival was 8.4 months, and the 1-year survival rate was 40% (Perez-Soler, 2004). A recently presented study with erlotinib at 150 mg as single agent in first line treatment of IIIB/IV NSCLC patients showed a non-progression rate of 55% after 6 weeks of treatment (Giaccone, 2005).

Based on the results of the single agent phase II studies, phase III studies in combination with chemotherapy were performed. In two large phase III studies (TALENT, TRIBUTE) analyzing treatment of erlotinib in combination with chemotherapy, in more than 2000 patients no benefit for the addition of erlotinib could be shown (Gatzemeier, 2004; Herbst, 2004).

Recently, the randomized, double blind, placebo controlled study performed by the National Cancer Institute of Canada evaluated 731 patients with locally advanced or metastatic (stage IIIB or IV) NSCLC after failure of one or more chemotherapy regimens. The proportion of patients who experienced an objective response in the erlotinib monotherapy group was higher than in the placebo group (8.9% versus 0.9%,  $p < 0.001$ ). Treatment with erlotinib was associated with significantly longer overall survival than placebo (median survival 6.7 months versus 4.7 months respectively) (Shepherd et al., 2005).

These data led to FDA approval in the US in November 2004. With the U.S label, Tarceva® (erlotinib) is indicated for all NSCLC patients after failure of at least one prior chemotherapy regimen. In 2005 Tarceva® has been approved in Switzerland and in the EU for the same indication.

### **Storage of Tarceva:**

Tarceva will be provided by Roche and stored at room temperature in a temperature controlled, locked locker in the outpatient department of the department of internal medicine I. Unlabeled Tarceva® as commercially available will be provided by Roche.

### **Administration of therapy**

Day 1-42 (week 1-6): Erlotinib (Tarceva®) 150 mg p.o. **once** daily,

It is recommended to administer Tarceva® 1 hour after meals. In addition, patients should avoid food ingestion for at least 2 hours after Tarceva®. For the same reason the administration of proton pump blockers is not recommended during therapy.

It is recommended to perform the following blood tests routinely once per week during erlotinib (Tarceva®) therapy:

EDTA blood: blood cell count

serum: creatinin, uric acid, bilirubin, gamma-GT, GOT, GPT

### **Side effects**

### **Reported erlotinib (Tarceva®) adverse reactions**

Clinically significant erlotinib (Tarceva®) adverse reactions:

1. Grade 3 to 4 **rash and diarrhea** occurred in 9% and 6% patients, respectively. The median time to onset of rash in a phase III clinical trial was 8 days and to onset of diarrhea 12 days (Shepherd et al., 2005).
2. **Liver function abnormality** - grade 2 ( $>2.5 - 5.0 \times \text{ULN}$ ) including elevated ALT, AST and bilirubin occurred in 4% of the patients treated with Tarceva and  $<1\%$  of placebo treated patients in a phase-III study. Grade 3 elevations were not observed in Tarceva® treated patients. During treatment with erlotinib, the patients should be monitored by liver function tests at least once every 1 to 2 months (Shepherd et al., 2005).
3. **Interstitial pneumonia** (interstitial lung disease – ILD) has been observed in a phase III study in NSCLC patients receiving erlotinib at an overall incidence of about 0.8 percent, which was not different to the placebo group. Among patients who developed ILD, symptoms began within 5 days to more than 9 months after erlotinib therapy initiation (median 47 days). The overall incidence of ILD in Tarceva® treated patients was reported to be approximately 0.6%. In the event of acute onset or worsening of pulmonary symptoms (dyspnea, cough, fever), erlotinib therapy should

be interrupted and a prompt diagnostics of these symptoms should start. If interstitial lung disease is confirmed, erlotinib should be discontinued and the patient should be treated appropriately (Shepherd et al., 2005).

Adverse reactions occurring in Tarceva®-treated patients (Shepherd et al., 2005)

| NCI CTC Grade        | Any Grade (%) | Grade 3 (%) | Grade 4 (%) |
|----------------------|---------------|-------------|-------------|
| Rash                 | 75            | 8           | <1          |
| Diarrhea             | 54            | 6           | <1          |
| Anorexia             | 52            | 8           | 1           |
| Fatigue              | 52            | 14          | 4           |
| Dyspnea              | 41            | 17          | 11          |
| Cough                | 33            | 4           | 0           |
| Nausea               | 33            | 3           | 0           |
| Infection            | 24            | 4           | 0           |
| Vomiting             | 23            | 2           | <1          |
| Stomatitis           | 17            | <1          | 0           |
| Pruritus             | 13            | <1          | 0           |
| Dry skin             | 12            | 0           | 0           |
| Conjunctivitis       | 12            | <1          | 0           |
| Keratoconjunctivitis | 12            | 0           | 0           |
| Abdominal pain       | 11            | 2           | <1          |

## Precautions

1. Potent inducers of CYP3A4 may reduce the efficacy of erlotinib whereas potent inhibitors of CYP3A4 may lead to increased toxicity. Concomitant treatment with these types of agents should be avoided.
2. Current smokers should be advised to stop smoking, as plasma concentrations could be reduced otherwise.
3. Cases of interstitial lung disease (ILD), including fatalities, have been reported uncommonly in patients receiving Tarceva for treatment of non-small cell lung cancer (NSCLC) or other advanced solid tumours.
4. If a **patient develops diarrhoea**, the patient should be managed appropriately by symptomatic treatment, dose reduction or temporary suspension of the treatment with

## INDIVIDUAL TRIAL PROCEDURE

erlotinib depending on the condition of the patient (see chapter 6.5 Treatment postponement, dose reductions and interruption).

5. In patients with elevated liver enzymes prior treatment (total bilirubin, ASAT, ALAT 2 x ULN) liver enzymes will be monitored twice weekly.

Precautions for co-administration with erlotinib (Tarceva®)

Tarceva® should be **administered with care** when co-administered with following drugs:

| Drug                                                                                                                                                                               | Effects                                                                                                                                                                                                                                           |
|------------------------------------------------------------------------------------------------------------------------------------------------------------------------------------|---------------------------------------------------------------------------------------------------------------------------------------------------------------------------------------------------------------------------------------------------|
| CYP3A4 inducers:
phenytoin, carbamazepine, rifampicin, barbiturates , etc.                                                                                               | Blood erlotinib concentration may be decreased , which may lead to decreased effects of the drug.                                                                                                                                          |
| CYP3A4 inhibitors:
azole antifungal agent (i.e. itraconazole), macrolide (i.e. erythromycin), ritonavir , indinavir, diltiazem and verapamil , etc. | Blood erlotinib concentrations may be increased , which may lead to increased incidence and severity of adverse drug reactions. Co-administration with itraconazole resulted in an 80% increase in the AUC of erlotinib.            |
| warfarin, cumarin (Marcumar)                                                                                                                                                | There were reports on INR elevations and bleeding events on co-administration with warfarin. When erlotinib is used concomitantly with warfarin, the patient should be monitored for prothrombine time or INR at regular intervals. |

## Restaging procedures during and after erlotinib therapy

### Examinations

Since the primary objective of the proposed study is to evaluate the accuracy of FDG-/FLT-PET analysis for early prediction of erlotinib non-progression in patients with NSCLC, the FDG- and FLT-PET examinations will be performed in exactly defined periods before, during and after therapy (s. table below).

| Time point                             | Imaging of involved areas       |
|----------------------------------------|---------------------------------|
| Between d-10 and d1 (prior to therapy) | FDG-PET, FLT-PET, CT            |
| Day 1                                  | Start of therapy with erlotinib |
| Between d7 and d14                     | FDG-PET and FLT-PET             |
| Week 7                                 | FDG-PET, FDG-PET, CT            |

In week 7 the following clinical and laboratory analyses will be performed:

- Clinical examination including physical examination:
  - height, weight, vital signs, ECOG performance status
- Assessment of the neurological status
- Existing signs and symptoms
- Concomitant medication
- Laboratory assessment including:
  - blood count including differential count
  - serum electrolytes (Na, K, Ca),
  - liver function parameters (total bilirubin, ASAT, ALAT, AP,  $\gamma$ GT, LDH),
  - renal function parameters (creatinine, BUN, uric acid),
  - ESR
  - CYFRA 21-1, CEA

These examinations may not include examinations which might be necessary if chemotherapeutic treatment is planned for progressive disease (see 5.7.6).

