## 2 AIM OF TRIAL

Based on the survival benefit demonstrated in patients with relapsed NSCLC (Shepherd et al., 2005) as well as on its favourable toxicity profile compared to chemotherapy the EGFR-TKI erlotinib represents an attractive candidate to be included also in protocols for the first line treatment of NSCLC. Accordingly, preliminary data from phase II trials show promising response rates for erlotinib treatment in the first line setting (Giaccone, 2005). In parallel, in the near future further targeted drugs will be available for NSCLC treatment. For instance, the addition of the anti-VEGF monoclonal antibody bevacizumab has recently shown to prolong survival when added to standard chemotherapy as first line treatment of NSCLC. Thus, in order to optimize the choice and the sequence of new drugs in NSCLC treatment, an early identification of patients with no clinical benefit, i.e. patients with progressive disease under treatment, is desirable. In the ERLOPET trial, we aim at establishing PET analysis as a tool for early identification of NSCLC patients with no clinical benefit from monotherapy with erlotinib as first line treatment. A pre-treatment computed tomography (CT) scan will be performed for evaluation of the patients' individual tumor burden. FDG- and FLT-PET scans will be performed between d -10 and d1 (but prior to therapy) for identification of pre-treatment PET status. Between d7 and d14, FDG- and FLT-PET scans will be performed for the early identification of erlotinib non responders. The imaging procedures will be performed at different days, i. e. one procedure per day. After six weeks of treatment, final response evaluation will be performed using CT, FDG- and FLT-PET scans. These results will be correlated to the mutational status of the EGFR - and the KRAS gene and the expression of EGFR in pretreatment samples.

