**Applied dose in each PET analysis:**

| Total activity for the respective RP | ED due to application of the RP | ED due to application of ALL the RP's | ED of all TM's | Allover ED                                 |
|--------------------------------------|---------------------------------|---------------------------------------|----------------|--------------------------------------------|
| Max. 370 MBq FDG
Day -4           | 7,0 mSv                         | 7 mSv                                 | 0,1 mS         | 7,1 mSv                             |
| Max. 300 MBq FLT
Day -3           | 9,9 mSv (f)
8,4 mSv (m)      | 16,9 mSv (f)
15,4 mSv (m)          | 0,1 mSv        | 17,0 mSv (f)
15,5 mSv (m) |
| Max. 370 MBq FDG
Day +8           | 7,0 mSv                         | 23,9 mSv (f)
22,4 mS (m)           | 0,1 mS         | 24,0 mSv
22,5 mSv         |
| Max. 300 MBq FLT
Day +9           | 9,9 mSv (f)
8,4 mSv (f)      | 33,8 mSv (f)
30,8 mSv (m)          | 0,1 mSv        | 33,9 mSv
30,9 mSv         |
| Max. 370 MBq FDG
Week 7           | 7,0 mSv                         | 40,8 mSv (f)
37,8 mSv (m)          | 0,1 mS         | 40,9 mSv
37,9 mSv         |
| Max. 300 MBq FLT
Week 7           | 9,9 (f) mSv
8,4 (m) mSv      | 50,7 mSv (f)
46,2 mSv (m)          | 0,1 mSv        | 50,8 mSv (f)
46,3 mSv (m) |

The used dose is the minimal dose to obtain high quality data suitable for further analysis

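### The three imaging schedule tables list FDG-PET twice and no FLT-PET in week 7, contradicting the aim section, the dose table and the sentence that introduces one of the tables

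*Protocol*

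**What the plan says.** The protocol prints the same imaging schedule three times: in section 0.4 (Flowsheet), as Table 1 in section 5.5, and under Examinations in the restaging part of section 5.9. Each copy lists both tracers at baseline and both again between days 7 and 14. For week 7 each copy reads "FDG-PET, FDG-PET, CT".

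Three other statements bear on week 7:

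- Section 2 (Aim of trial) says: "After six weeks of treatment, final response evaluation will be performed using CT, FDG- and FLT-PET scans".
- The dose table in section 5.6 has two week-7 rows, "Max. 370 MBq FDG Week 7" and "Max. 300 MBq FLT Week 7".
- The sentence that introduces the section 5.9 table says that "the FDG- and FLT-PET examinations will be performed in exactly defined periods before, during and after therapy", and sends the reader to the table for the times.

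Section 3.1 describes secondary objectives 1 to 3 (PET characteristics of progression, response and stable disease) in terms of SUV change during treatment, without naming a time point.

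**The concern.** The schedule table is what staff work from when booking scans, and section 5.9 makes it the operative instruction for PET timing. All three copies carry the same week-7 entry, so comparing one copy with another does not expose the problem. It shows only when the tables are read against section 2, the dose table or the introductory sentence in section 5.9.

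At stake is the week-7 FLT measurement. A scan not done in week 7 cannot be recovered later. Without it, the six-week evaluation has no FLT component, and no FLT change from baseline to week 7 can be computed for secondary objectives 1 to 3. Section 5.9 also names PET among the examinations that document tumor control at the week-7 restaging, so it should be clear which PET scans exist at that point.

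**Working it through.** This is a conflict of text, so no power or error-rate calculation applies. The one linked figure is the cumulative tracer dose in section 5.6, which shows what set of injections the dose table was built on.

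**Inputs (section 5.6 dose table).** FDG 7.0 mSv per injection. FLT 9.9 mSv per injection for women and 8.4 mSv for men. In the day +9 row both FLT figures carry the label for women. I read 8.4 as the value for men, as in the other FLT rows, and the running total confirms it (22.4 + 8.4 = 30.8).

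**Step 1: reproduce the stated totals.** The order is FDG, FLT at baseline; FDG, FLT early; FDG, FLT in week 7.

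| After injection | Women (mSv) | Men (mSv) |
|---|---|---|
| FDG, day −4 | 7.0 | 7.0 |
| FLT, day −3 | 16.9 | 15.4 |
| FDG, day +8 | 23.9 | 22.4 |
| FLT, day +9 | 33.8 | 30.8 |
| FDG, week 7 | 40.8 | 37.8 |
| FLT, week 7 | 50.7 | 46.2 |

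In closed form: 3 × 7.0 + 3 × 9.9 = 50.7 and 3 × 7.0 + 3 × 8.4 = 46.2. Every running total matches the protocol. The last column of the dose table adds 0.1 mSv, giving 50.8 and 46.3, which also matches.

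**Step 2: apply the schedule tables as printed.** FDG: 1 + 1 + 2 = 4. FLT: 1 + 1 + 0 = 2.

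- Women: 4 × 7.0 + 2 × 9.9 = 47.8 mSv, which is 50.7 − 47.8 = 2.9 mSv below the stated total.
- Men: 4 × 7.0 + 2 × 8.4 = 44.8 mSv, which is 46.2 − 44.8 = 1.4 mSv below the stated total.

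Both readings have six injections. They differ only in the tracer used for one of the two week-7 scans.

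**Step 3: what each reading leaves for analysis.**

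| Quantity | One FDG + one FLT in week 7 | Schedules read literally |
|---|---|---|
| Baseline and day 7–14 SUV, both tracers | available | available |
| Week-7 FDG SUV | available | available |
| Week-7 FLT SUV | available | absent in every patient (0 of 40) |
| Week-7 CT for RECIST | available | available |

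The primary objective concerns early prediction. Section 2 assigns that to the early scans ("Between d7 and d14, FDG- and FLT-PET scans will be performed for the early identification of erlotinib non responders"), and all three schedules list both tracers in that window.

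**The case against.** The strongest reply is that nobody would carry out the row as printed. Table 1 is titled as a schedule for CT and both tracers, the sentence introducing the section 5.9 table names both tracers after therapy, and no section gives a purpose for two FDG scans in week 7. The trial is single-center, and its own dose table gives a correctly structured, time-ordered list of injections. On this view it is a copied typing error. That stands as an explanation and makes the loss less likely. It does not remove the contradiction, which nothing in the protocol corrects.

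A reader might infer three stronger things that the protocol does not support:

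- *That secondary objectives 1 to 3 cannot be met without a week-7 FLT scan.* Section 3.1 refers only to SUV change during treatment, and section 7.3 ties the expected SUV reduction to the scans on days 8 and 9. The change from baseline to days 7–14 remains available for both tracers. Only the week-7 FLT component is at risk.
- *That patients would be exposed to extra radiation.* The second week-7 FDG injection does not appear in the dose table, but it replaces an FLT injection. The number of injections stays at six and the total tracer dose falls.
- *That the primary result or the response classification is compromised.* Neither depends on week-7 FLT. The early scans are scheduled correctly, and RECIST response is measured on CT.

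**Conclusion.** The contradiction is real and is wrong as written. Three copies of the operative schedule disagree with the aim section, with the dose table and, in section 5.9, with the sentence that introduces the table. The dose totals were built on one FDG and one FLT injection in week 7, since they reproduce exactly on that basis and miss by 2.9 mSv (women) and 1.4 mSv (men) on the printed schedule.

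The consequence is limited and conditional. If the tables are followed literally, the FLT part of the six-week evaluation is missing in all 40 planned patients, and with it any baseline-to-week-7 FLT change. That rests on the assumption of literal execution, which is uncertain for a likely copying error at one center. The point merits correction because the entry sits in the working schedule and the fix is very cheap. It does not threaten the primary analysis.

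**What to change.** Reconcile the week-7 row in section 0.4, in Table 1 of section 5.5 and in the restaging table of section 5.9 with section 2, with the dose table in section 5.6 and with the introductory sentence in section 5.9. Schedule, aim and dose table should then describe one and the same set of week-7 scans. If patients have already reached week 7 under the printed tables, record which tracers were actually given, so that the analysis knows where a week-7 FLT value exists.

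The cost is three table cells. If they are aligned with the scans already in section 2 and the dose table, no new procedure is added, and the sample size and the analysis do not change.
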